APPENDIX A (cont’d)

Psoriasis Area and Severity Index (PASI)

|  | Erythema a | Scaling | Thickness |
| --- | --- | --- | --- |
| 0=none | No redness | No scaling | No elevation over normal skin |
| 1=slight | Faint redness | Fine scale partially covering lesions | Slight but definite elevation, typically edges indistinct or sloped |
| 2=moderate | Red coloration | Fine to coarse scale covering most of all of the lesions | Moderate elevation with rough or sloped edges |
| 3=severe | Very or bright red coloration | Coarse, non-tenacious scale predominates covering most or all of the lesions | Marked elevation typically with hard or sharp edges |
| 4=very severe | Extreme red coloration; dusky to deep red coloration | Coarse, thick, tenacious scale over most or all lesions; rough surface | Very marked elevation typically with hard sharp edges |
| a Does not include residual hyperpigmentation, hypopigmentation, pigmented macules, or diffuse slight pink coloration as erythema. | | | |

APPENDIX A (cont’d)

Psoriasis Area and Severity Index (PASI)

Calculating PASI

To calculate the PASI, the sum of the severity rating for the three main signs will be multiplied with the numerical value of the area affected and with the various percentages of the four body areas. These values will then be added to complete the formula as follows:

| PASI = | 0.1 (Eh  Th  Sh) Ah  0.3 (Et  Tt  St) At   0.2 (Eu  Tu  Su) Au  0.4 (El  Tl  Sl) Al |
| --- | --- |

| Row |  | Head | Trunk | | Upper Limbs | Lower Limbs | |  |
| --- | --- | --- | --- | --- | --- | --- | --- | --- |
| 1 | Erythema a |  |  | |  |  | |  |
| 2 | Thickness a |  |  | |  |  | |  |
| 3 | Scaling a |  |  | |  |  | |  |
| 4 | Total each column |  |  | |  |  | |  |
| 5 | Degree of involvement b |  |  | |  |  | |  |
| 6 | Multiply Row 4 by Row 5 |  |  | |  |  | |  |
| 7 |  |  0.10 |  0.30 | |  0.20 |  0.40 | |  |
| 8 | Multiply Row 6 by Row 7 |  |  | |  |  | |  |
| 9 | Total PASI (add together each column from Row 8) | | |  | | |  | |
| a Rank severity of psoriatic lesions: 0=none, 1=slight, 2=moderate, 3=severe, 4=very severe.  b Rank area of psoriatic involvement: 0=none, 1= <10%, 2=10% to <30%, 3=30% to <50%, 4=50% to <70%, 5=70% to <90%, 6=90% to 100%. | | | | | | | | |

APPENDIX B

LINEAR PASI

| Row |  | Head | Trunk | | Upper Limbs | Lower Limbs |  |
| --- | --- | --- | --- | --- | --- | --- | --- |
| 1 | Erythema a |  |  | |  |  |  |
| 2 | Thickness a |  |  | |  |  |  |
| 3 | Scaling a |  |  | |  |  |  |
| 4 | Total each column |  |  | |  |  |  |
| 5 | % of involvement |  |  | |  |  |  |
| 6 | Multiply row 4 by 5 |  |  | |  |  |  |
| 7 | Factor | 0.6 | 1.8 | | 1.2 | 2.4 |  |
| 8 | Multiply Row 6 by Row 7 |  |  | |  |  |  |
| 9 | Total PASI (add together each column from Row 8) | | |  | | |  |
| a Rank severity of psoriatic lesions: 0=none, 1=slight, 2=moderate, 3=severe, 4=very severe | | | | | | | |

This worksheet is a modification of a conventional PASI. Scaling, erythema, and thickness are determined in the same fashion and using the same descriptors as in the conventional PASI. The modification here is that the actual percentage involvement of head, trunk, and limbs is recorded so that increases or decreases in surface extent impact upon the PASI score in a 1:1 (or linear) fashion. For example, a decrease in surface involvement by 50% (but residual lesions have same erythema, thickness, and scale as baseline) would produce a 50% reduction in the linear PASI measure. The scale has been adjusted (by factors in row 7) so that the scale produces a measure from 0-72, as does the conventional PASI measure.

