**G) Study design**

materials and methods

Subject Selection

All subjects volunteering for participation in the study will be screened using the following inclusion and exclusion criteria. Approximately 30 subjects with moderate to severe plaque psoriasis will be entered into the study.

Inclusion Criteria

Subjects must meet the following inclusion criteria to be eligible for study entry:

- Signed informed consent
- Plaque psoriasis covering >10% of total BSA
- Diagnosis of plaque psoriasis for at least 6 months
- PASI score >=12 (see Appendix A) or Linear PASI score of >= 8.0 at screening (see Appendix B).
- In the opinion of the investigator, candidate for systemic therapy for psoriasis:

A. Who has not been previously treated (naive to systemic treatment) OR

B. Who has had prior treatment with systemic therapy for psoriasis (e.g., PUVA, cyclosporine, corticosteroids, methotrexate, oral retinoids, mycophenolate mofetil (MMF), thioguanine, hydroxyurea, sirolimus, azathioprine, 6‑MP, etanercept)

- Body weight of <140 kg
- 18 to 75 years old. As the risk of Efalizumab in childhood is unknown, those < 18years will be excluded from the study.
- For women of childbearing potential or in men whose partners may become pregnant, willingness to use an acceptable method of contraception to prevent pregnancy for the duration of the study (while receiving study medication and 3 months following). Acceptable methods of contraception include use of a condom; abstinence; use by sexual partner of oral implantable or injectable contraceptives, IUD, female condom, diaphragm with spermicide, cervical cap; or a sterile sexual partner
- Willingness to hold sun exposure reasonably constant and to avoid use of tanning booths or other UV light sources during the study

Exclusion Criteria

Subjects who meet any of the following exclusion criteria are ineligible for study entry:

- Guttate, erythrodermic, or pustular psoriasis as sole or predominant form of psoriasis
- History of severe allergic or anaphylactic reactions to humanized monoclonal antibodies or fusion proteins that contain an Ig Fc region
- Clinically significant psoriasis flare during screening or on the first treatment day
- Treatment with efalizumab (anti-CD11a) within the last 12 months before enrollment
- Pregnancy or lactation. As the risk of Efalizumab in pregnancy is unknown, pregnant women will be excluded from the study.

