**APPENDIX A**

**Psoriasis Area and Severity Index (PASI)**

Evaluator Requirements

 The evaluator must be a dermatologist or an experienced health care provider.

 The evaluator must have attended the Investigator meeting or have been trained by someone who attended the Investigator meeting.

 The same evaluator should determine all PASIs for any individual subject throughout the trial.

A backup evaluator is only allowed in case of emergency or special situation when the designated evaluator is unable to perform the evaluation. The backup evaluator must be a dermatologist or an experienced health care provider and have attended the Investigator meeting or have been trained by someone who attended the Investigator meeting.

General Instructions

1. For each area of the body, rate erythema, scaling, and thickness for the **average** plaque or the overall condition of plaques in that region.

2. Rate plaques as they are actually seen on the day of examination. Do not rate in comparison with baseline condition.

PASI Scoring

PASI scores can range from 0 to 72. Dermatologic disease severity is to be scored as follows:

Body Areas

Four main body areas will be assessed, the head (h), the trunk (t), the upper extremities (u), and the lower extremities (l) corresponding to 10%, 30%, 20%, and 40% of the total body surface area (BSA), respectively.

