APPENDIX C

Psoriatic Body Surface Area (BSA)

The percentage of total body surface area (BSA) affected by psoriasis is to be calculated using the following table.

| Body Segment | % of Total BSA | Anterior Sites Affected  (% of Total BSA) a | Posterior Sites Affected  (% of Total BSA) a | Row Percentage Total |
| --- | --- | --- | --- | --- |
| Head | 10% | __________  __________ | | ___ % |
| Trunk | 30% | __________  __________ | | ___ % |
| Upper limbs | 20% | __________  __________ | | ___ % |
| Lower limbs | 40% | __________  __________ | | ___ % |
| Total | 100% |  | | ___ % |
| a Percentage of body surface affected by psoriasis (total of all affected segments). | | | | |

The first column of the table lists the four segments of the body (see Appendix A, Psoriasis Area and Severity Index, for assignment of body segments). The second column lists the approximate percentage of the entire body area represented by each segment. This percentage is to serve as a reference and represents the maximal area that can be reported in the fifth column. Using the “rule of palm” (1% BSA = palm to first interphalangeal joint), Columns 3 and 4 are to be determined. The rule of palm reference is determined based on the size of the subject’s palm and not the evaluator’s palm. Note: The percentage of anterior portion and percentage of posterior portion affected by psoriasis are to be determined as percentages of the total BSA. Column 5 is used to sum the totals of the four body segments to calculate the total BSA.

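### The Linear PASI worksheet in Appendix B reaches its stated 0-72 range only if row 5 is a proportion, but row 5 is labelled as a percentage

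*Protocol*

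**What the plan says.** Appendix B (Linear PASI) builds the score in rows. Erythema, thickness and scaling are each graded 0 to 4 in four body regions ("Rank severity of psoriatic lesions: 0=none, 1=slight, 2=moderate, 3=severe, 4=very severe") and summed in row 4. Row 5 is headed as a percentage of involvement, and the text explains that "the actual percentage involvement of head, trunk, and limbs is recorded". Row 6 is "Multiply row 4 by 5". Row 7 is "Factor | 0.6 | 1.8 | | 1.2 | 2.4" for head, trunk, upper limbs and lower limbs. The regional products are added to give the total. The text then says the row 7 factors were set "so that the scale produces a measure from 0-72, as does the conventional PASI measure". Appendix A gives the same range for the conventional score: "PASI scores can range from 0 to 72".

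The score is used in two places. The Inclusion Criteria under Study design require "PASI score >=12 (see Appendix A) or Linear PASI score of >= 8.0 at screening (see Appendix B", alongside a separate requirement of more than 10% of total BSA. The secondary outcomes list the linear PASI as a measure of overall clinical response at weeks 6 to 24.

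**The concern.** The form's label and its stated range cannot both be followed. Someone who writes 15 under a percentage heading for 15% involvement, then multiplies as directed, gets a score 100 times what the 0-72 scale would give. Nothing on the form prints the missing step.

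Two uses are exposed. The first is eligibility: Linear PASI is one arm of an either/or severity criterion, and a threshold of 8.0 means something quite different on a 0-7200 scale. The second is the secondary outcome: if some forms were completed in percent and others in proportions, the scores could not be pooled or compared. With about 30 patients planned, a few such forms would matter.

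**Working it through.** **Inputs.** Row 4 runs from 0 to 12 (three signs, each 0 to 4; Appendix B). The row 7 factors are 0.6, 1.8, 1.2 and 2.4 (Appendix B). The region weights are 0.1, 0.3, 0.2 and 0.4 (Appendix A). The entry thresholds are PASI at least 12 or Linear PASI at least 8.0, and BSA above 10% (Inclusion Criteria).

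**Formula.** Linear PASI = sum over regions of factor x sign total x row 5 entry.

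**Step 1: reproduce the stated range.** The factors sum to 0.6 + 1.8 + 1.2 + 2.4 = 6.0, and each is 6 times its region weight. With full involvement entered as 1, the maximum is 12 x 1 x 6.0 = 72. This is the stated figure.

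**Step 2: the form as labelled.** With full involvement entered as 100, the maximum is 12 x 100 x 6.0 = 7200.

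**Step 3: what this does to the 8.0 threshold.** Each factor is 6 times the region's share of the body. So if the sign total S is the same in every affected region, the score is 6 x S x BSA, wherever the disease lies.

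| Sign total S | Score at 10% BSA, percent entry | Score at 10% BSA, proportion entry | BSA needed for 8.0, proportion entry |
| --- | --- | --- | --- |
| 1 | 60 | 0.6 | not reachable (133%) |
| 3 | 180 | 1.8 | 44.4% |
| 6 | 360 | 3.6 | 22.2% |
| 9 | 540 | 5.4 | 14.8% |
| 12 | 720 | 7.2 | 11.1% |

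With percent entry, the lowest score at 10% BSA with any active sign is 60, so the 8.0 limit removes nobody who meets the BSA criterion. With proportion entry, a patient at 10% BSA scores at most 7.2, so the limit restricts entry beyond the BSA rule.

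**Step 4: a patient for whom the unit decides.** Take 15% involvement in every region with a sign total of 5. BSA is 15%, which meets that criterion. The conventional area grade is 2 (10% to below 30%), so PASI = 5 x 2 x 1.0 = 10, below 12. Linear PASI with proportions is 5 x 0.15 x 6.0 = 4.5, below 8.0. With percentages it is 5 x 15 x 6.0 = 450. The patient fails the severity criterion on the stated scale and passes it on the form as labelled.

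**Step 5: would the error be visible?** At screening, usually yes: at 10% BSA, percent entry already gives 60 with S = 1 and 120 with S = 2. Late in treatment, not always: 2% involvement throughout with S = 3 gives 3 x 2 x 6.0 = 36 in percent and 0.36 as a proportion. The 36 lies inside 0-72.

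**The case against.** The best defence is that the unit can be worked out. 100% equals 1.0, nothing tells staff in so many words to enter whole numbers, and both the stated range and the construction of the factors point to proportions. That stands, and it is why neither the range nor the threshold is at fault. It does not rescue the form: under a percentage heading, 10% is naturally written as 10, and the text credits the row 7 factors alone with producing 0-72. That credit is correct only with a division by 100 that is not printed.

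It can also be said that misuse would be noticed, since most screening scores would exceed 72 and conventional PASI is recorded at the same visits. This largely stands for screening, less so for low scores on treatment. Candidacy for systemic therapy is a further entry requirement, so severity would not go wholly unchecked.

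The effect on outcomes is limited. Linear PASI is not a primary outcome. If one unit is used throughout, a constant factor of 100 leaves percentage changes and rankings untouched, and Appendix B's own example of a 50% reduction is unaffected. Appendix A also asks for one evaluator per subject for the PASI.

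A reader might go further and suspect that Appendix C figures, which "are to be determined as percentages of the total BSA", would be copied into row 5. Region size would then count twice, and the maximum would fall to 12 x 6 x (0.01 + 0.09 + 0.04 + 0.16) = 21.6 as proportions, or 2160 in percent. The documents do not support this as a finding. Appendix B speaks of involvement of the head, trunk and limbs, which implies a regional denominator, and nothing directs staff to transfer the Appendix C numbers.

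**Conclusion.** Appendix B is internally inconsistent. Completed as labelled it spans 0-7200; the stated 0-72 requires row 5 to be a proportion. The discrepancy is a factor of 100. Read literally, it makes the 8.0 alternative non-selective for anyone with more than 10% BSA and any active sign; on the stated scale the cut-off does restrict entry. The BSA figures in the table assume the same sign total in all affected regions. The minimum of 60 needs only a sign total of at least 1 wherever there is disease.

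A reader might infer that the trial enrolled patients without regard to severity, or that scores were wrongly recorded. The documents show neither: the intended scale can be recovered, literal entry would usually be conspicuous, and no completed scores are reported. This is a minor error of units in a scoring form that is in operational use.

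**What to change.** Make one of two equivalent changes to Appendix B. Either relabel row 5 as the proportion of this body region involved (0.00 to 1.00), or keep percentages and divide the row 7 factors by 100, giving 0.006, 0.018, 0.012 and 0.024. The check is then 12 x 100 x 0.06 = 72. Making both changes would put the score too low by a factor of 100.

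State in the Inclusion Criteria that the Linear PASI threshold of 8.0 refers to the resulting 0-72 scale. Add a note to Appendix B that the denominator is the body region, unlike Appendix C, which uses total BSA. Check that any scores already recorded lie on the 0-72 scale, looking also at low on-treatment values, where a percent entry need not exceed 72.

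The cost is a one-line correction to the worksheet, two clarifying sentences and a check of existing forms. No new data are needed and the threshold does not change.

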APPENDIX C

Psoriatic Body Surface Area (BSA)

The percentage of total body surface area (BSA) affected by psoriasis is to be calculated using the following table.

| Body Segment | % of Total BSA | Anterior Sites Affected  (% of Total BSA) a | Posterior Sites Affected  (% of Total BSA) a | Row Percentage Total |
| --- | --- | --- | --- | --- |
| Head | 10% | __________  __________ | | ___ % |
| Trunk | 30% | __________  __________ | | ___ % |
| Upper limbs | 20% | __________  __________ | | ___ % |
| Lower limbs | 40% | __________  __________ | | ___ % |
| Total | 100% |  | | ___ % |
| a Percentage of body surface affected by psoriasis (total of all affected segments). | | | | |

The first column of the table lists the four segments of the body (see Appendix A, Psoriasis Area and Severity Index, for assignment of body segments). The second column lists the approximate percentage of the entire body area represented by each segment. This percentage is to serve as a reference and represents the maximal area that can be reported in the fifth column. Using the “rule of palm” (1% BSA = palm to first interphalangeal joint), Columns 3 and 4 are to be determined. The rule of palm reference is determined based on the size of the subject’s palm and not the evaluator’s palm. Note: The percentage of anterior portion and percentage of posterior portion affected by psoriasis are to be determined as percentages of the total BSA. Column 5 is used to sum the totals of the four body segments to calculate the total BSA.

**APPENDIX D**

Tuberculosis (TB) Assessment

Tuberculin skin testing (purified protein derivative [PPD]) or a chest X-ray will be performed for the following high‑risk individuals:

 Individuals having close contact with individuals with active TB

 Individuals with a history of injection drug abuse

 Individuals with insulin‑dependent diabetes mellitus, silicosis, post‑gastrectomy, or jejunoileal bypass

 Individuals on prolonged (>3 months) high‑dose (systemic) corticosteroids (including inhalers) or other immunosuppressive therapies (e.g., methotrexate, cyclosporine, prednisone)

 Individuals with a body weight <90% of ideal body weight

 Individuals who live in institutional (high‑congregate) settings or shelters

 Individuals who are foreign‑born from Asia, Africa, or Latin America

 Individuals who are healthcare workers

Individuals with a history of bacille Calmette‑Guerin vaccination are required to have a chest X‑ray instead of PPD or to be able to document a negative chest X‑ray within the last year. The PPD skin test must be read between 48 and 72 hours.

Individuals with a newly positive TB skin test or chest X-ray are not eligible for enrollment. Individuals with an abnormal chest X‑ray showing fibrotic lesions consistent with previous TB are ineligible.

APPENDIX E

Study Drug Reconstitution and Administration

Study Drug Shipping and Packaging

The kits shipped to the study site will contain six vials of study drug. During the study each kit should be used for only 1 subject, but each subject will require more than one kit. Each vial will contain ~125 mg of study drug (efalizumab). If the packaging is damaged upon receipt or any unusual attributes or appearance of the study kits is observed, the kits should not be used and the problem should be immediately reported.

General Information and Instructions

 Vials should be refrigerated at 20C–80C (360F–460F). Do not freeze or store at room temperature. After reconstitution, vials should be handled gently to avoid foaming. Do not vortex. All transfer procedures must strictly adhere to aseptic technique.

 For safety, diphenhydramine hydrochloride for injection or another comparable antihistamine and epinephrine 1:1000 or 1:10,000 must be available at the site.

Reconstitution

1. Using an alcohol swab, wipe the rubber stopper of the Sterile Water for Injection (SWFI) and each vial of lyophilized study drug.

2. Using a 3‑cc syringe with 25‑gauge needle, withdraw 1.3 mL of sterile water from the SWFI vial.

3. Slowly withdraw the needle from the SWFI vial, being careful not to put pressure on the syringe plunger, and put the vial of SWFI down.

4. Leaving the vial of study drug on a firm surface, slowly puncture the rubber seal with the needle and syringe filled with SWFI.

5. Gently push down on the plunger to release the entire 1.3 mL of SWFI into the vial of lyophilized study drug.

6. Gently swirl the contents of the vial until contents have dissolved. Wait 5 minutes for the contents to completely dissolve. Do not shake the vial or “vortex” the contents.

7. Slowly withdraw the needle from the vial of study drug.

APPENDIX E (cont’d)

Study Drug Reconstitution and Administration

8. If more than one vial of study drug is required, repeat Steps 2–6.

9. Using a new alcohol swab, wipe the rubber stopper of the vial of reconstituted study drug.

10. Hold the vial of study drug upside down and insert a **3‑cc syringe** with a **25‑gauge needle** to retrieve the reconstituted drug product solution. If the injection volume is <1.0 mL, a 1‑cc syringe should be used in place of the 3‑cc syringe for the injection.

11. Remove the syringe and needle from the vial. To remove air trapped in between the needle and the drug, keep the needle pointed up and gently apply pressure to the plunger until a small amount of drug comes out of the needle.

12. If more than one vial of study drug is required per dose (the injection volume is >1.3 mL), repeat Steps 9 and 10.

Administration of Study Drug

 Administer by subcutaneous injection in the upper arm, thigh, buttock, or abdomen. Injections should be rotated systematically among the sites.

 No more than 1.5 cc of test article should be administered per injection; therefore, some subjects may require two or more injections to deliver the assigned dosage. If more than one injection is required, the test article should be divided equally among the syringes.

**APPENDIX F**

**Research Blood Tests**

1. **IMMUNOHISTOCHEMISTRY AND IMAGE ANALYSIS**

Tissue sections will be stained with haematoxylin and eosin (H&E) and with purified mouse anti-human monoclonal antibodies to K16, CD3, CD8 and CD103. Biotin-labeled horse anti-mouse antibody will be used for amplification, with avidin-biotin complex and developed with chromogen 3-amino-9-ethylcarbazole. Epidermal thickness measures will be computed using National Institute of Health software (NIH Image 6.1), and positive cells will be counted manually using computer-assisted image analysis. Conformational states of LFA-1 will be analyzed where there are suitable antibodies available for immunohistochemistry.

1. **RT-PCR ANALYSIS**

The PAXgene Blood RNA System is a commercially available integrated and standardized system for the collection and stabiization of whole blood specimens and isolation of cellular RNA. As an alternative, CPT tubes may also be used for this purpose. We will collect blood samples at time points indicated in Appendix I. Genes of interest include inflammatory genes and those responsible for the phenotype of psoriasis (-IFN, TNF-, STAT-1, iNOS, IL-8, MIG, IP-10, IL-19, IL-20, IL-23); those representative of T-cell activation (IFN-, IL-12, CD25); dendritic cell activation (CD80, IL-12); keratinocyte proliferation (Keratin 16); Type 1 or Type 2 T-cell immune deviation (-IFN , IL-4, IL-10, IL-11) and new genes discovered from gene chip data (ENRAGE, MMP). Other genes may be studied as they are discovered or their relevance is newly appreciated.

RNA will be extracted from tissues frozen in liquid nitrogen using the RNeasy Mini Kit. The primers and probes for the TaqMan RT-PCR assays for chosen genes have been generated using the Primer Express algorithm, version 1.0, using published genetic sequences (NCBI-PubMed) for each gene. The RT-PCR reaction will be performed using EZ PCR Core Reagents according to the manufacturer's directions. The samples will be amplified and quantified on an Applied Biosystems PRISM 7700 using the following thermal cycler conditions: 2 min @ 50C; 30 min @ 60 C; 5 min @ 95C; and 40 cycles of 15 sec @ 95C followed by 60 sec @ 60C. The human acidic ribosomal protein (hARP) gene, a housekeeping gene, will be used to normalize each sample and each gene. The data will be analyzed and samples quantitated by the software provided with the Applied Biosystems PRISM 7700 (Sequence Detection Systems, ver.1.7).

1. **GENE EXPRESSION**

Gene chip studies will be performed as previously published by our group (Ostreicher et al, *The Pharacogenomics Journal,* 2001, 1, 272-287). Total RNA will be isolated from one half of a 6 mm full thickness skin biopsy using the Rneasy mini kit (Qiagen) and amplified using RiboAmp OATM RNA Amplification Kit (Arcturus). Labeled microarray targets will be prepared, and these will be hybridized to oligonucleotide arrays comprised of 12 000 known human genes (HuGeneU95 Av2, Affymetrix), for detection of fluorescence. Data analysis will be performed on raw fluorescent intensity values using GENECHIP 3.2 software (Affymetrix) or GeneTrafficTM.

1. **SATURATION ASSAY**

This competitive assay is performed by incubating PBMCs obtained during and after treatment with an anti-CD11a antibody (clone 25.3, Immunotech) which recognizes a different epitope than efalizumab. Stained cells will be analyzed by FACS to determine the percent binding with efalizumab.

1. **VLA-4 BINDING TO FIBRONECTIN AND ICAM-1**

Our laboratory will collaborate with [name] to confirm a previous finding in a small group of patients of decreased binding of T-cells to fibronectin, a VLA-4 ligand.

1. **T-CELL ACTIVATION ASSAYS**

T-cell activation will be assessed using a variety of techniques that are described below. We will need to work out methods so that down-regulation of surface receptors , e.g., LFA-1, TCR chains, and CD2, is maintained during an in vitro assay. Short-term activation-related assays (activation assessed within 4-6 hours) can probably be done on purified cell populations, but longer term assays will probably need to be done in whole blood preps or in purified cell populations to which autologous serum or efalizumab antibodies at an expected serum concentration is added. In turn, we need to establish a time-course for re-expression of various surface proteins after incubation in vitro with cells “washed” of exogenous or free efalizumab. Since we have not been able to reproduce receptor down-regulation by in vitro incubation of PBMC preps with exogenous efalizumab, we must work out re-expression kinetics and assay conditions on the first several patients that will be entered into this trial.

